### Individual recruitment

In partnership with the SME, the local research officers will conduct introductory sessions with the employees including a short presentation describing the purpose of the research. The local research officers will emphasise that participation is voluntary, and employers will not be notified about who is participating within their organisation. Participants will also be informed that they can withdraw from the research at any time without repercussions. Participants will also be given the opportunity to ask any questions they may have. The research officer will provide information on who to contact and how to contact them for any support or assistance. All employees will receive a link to the information sheet and an informed consent form.

For the intervention group, the local research officer will also explain the registration process for access to the MENTUPP Hub and what materials are available on the Hub. For the control group, the local research officer will explain that they will be given access to the MENTUPP Hub at the end of the study period.

### Implementation

The MENTUPP Hub is designed to be accessed by employees and their leaders who have completed the baseline questionnaires on a personal or work electronic device. Given the multi-level approach underpinning the intervention, the MENTUPP project is dependent on achieving buy-in from management within each SME. SMEs are advised to allow participants the opportunity to access and engage with the MENTUPP Hub during work hours, on average 20 min per week throughout the project. Participants can also access the Hub at any time and engage with the material at their own pace during their free time. To promote the intervention within each organisation, SMEs will be encouraged to designate a ‘Champion’ within their organisation. The local research officer will work with the ‘Champion’ by following a standardised method in the form of a series of checklists to encourage discussion and to determine the best approach to implementing the intervention within each organisation. This will ensure that all organisations have flexibility to implement the intervention in the most suitable way for them while still adopting a standardised approach across the nine intervention countries. The ‘Champion’ will determine the best methods for promoting engagement within the organisation and will be involved in boosting participation and retention at all levels. They will disseminate information from research officers to all employees and leaders within the organisation and provide feedback on any challenges or queries to research officers. Standardised information will include email templates and SMS text reminders to access the MENTUPP Hub and complete follow-up surveys. SMEs and participants within SMEs can withdraw their participation at any point of the study without repercussions. Participants can withdraw their data by contacting their local research officer and referring to their unique code.

If any changes are required to the recruitment, implementation or evaluation procedure due to unforeseen circumstances, this will be discussed at weekly implementation meetings with the local research officers. Any modifications required will be noted in the Standard Operating Procedure. Any major modifications will be noted to the funding agency.

### Data collection

Quantitative and qualitative measures will be utilised to collect all necessary data for outcome evaluation, process evaluation, and economic evaluation of the MENTUPP intervention. Measures were selected based on the Theory of Change (ToC) expected as a result of the intervention [66]. An overview of assessment is presented in Fig. 4 and further detailed information is presented in Table 1.

**Fig. 4 Fig4:**
[figure not shown]
SPIRIT figure of MENTUPP study protocol

**Table 1 Tab1:** Overview of measures, evaluation and outcomes

Type of evaluation			Concept	Type of outcomes / perspective	Outcome	Measure											Time of data collection		
**Outcome**	**Proce** **ss**	**Economic**				**Validated scales**						**Bespoke survey**							
						**WHO**	**PHQ-9**	**GAD-7**	**BAT**	**DSS**	**COPSOQ**	**Pre**	**Post**	**Monitoring**	**User data**	**Focus groups**	**Baseline**	**6 months**	**9 months**
X		X	Effectiveness	Long-term Outcomes	Improved wellbeing	X											X	X	X
X		X			Reduced mental illness: depression, anxiety, and burnout		X	X	X								X	X	X
X		X			Reduced personal stigma towards mental illness					X							X	X	X
X					Reduced productivity loss							X	X				X	X	X
		X			Support provided to employees facing mental health difficulties							X	X				X	X	X
		X			Attitudes to search for psychological support							X	X				X	X	X
X				Intermediate Outcomes	Improved psychosocial factors in the workplace						X						X	X	X
X					Improved support of employees facing mental health difficulties						X	X	X				X	X	X
X					More inclusive atmosphere promoting positive psychosocial factors							X	X				X	X	X
X					Improved attitudes to search for psychological support							X	X				X	X	X
X				Proximate Outcomes	Employees and leaders have increased knowledge on mental wellbeing, mental illness and stigma							X	X				X	X	X
X					Employees and leaders have enhanced skills to promote mental health, deal with mental illness and prevent stigma							X	X				X	X	X
X					Employees and leaders have more positive attitudes towards mental illness and help-seeking							X	X				X	X	X
X					Leaders have enhanced skills to address mental illness and prevent mental harm							X	X				X	X	X
X	X				The MENTUPP intervention is implemented as intended									X			X	X	X
	X				Reach									X			X	X	X
															X			X	X
	X				Adoption									X			X	X	X
																X		X	
	X				Implementation									X			X	X	X
																X		X	X
	X				Appropriateness											X		X	X
	X				Feasibility										X			X	X
	X				Maintenance									X			X	X	X
												X	X						
		X	Costs	Employer, Societal	Time spent by employers and employees on activities related to MENTUPP									X			X	X	X
												X	X						
		X		Employer, Societal	Time spent by employers and employees on the MENTUPP Hub										X			X	X
		X		Employer, Societal	Absenteeism of employees due to mental health issues							X	X				X	X	X
		X		Employer, Societal	Presenteeism of employees due to mental health issues							X	X				X	X	X
		X		Healthcare	Use of primary healthcare due to physical health issues							X	X				X	X	X
		X		Healthcare	Use of primary healthcare due to mental health issues							X	X				X	X	X
		X		Societal	Time investment of ROs to implement MENTUPP									X			X	X	X
		X		Societal	Travel costs of ROs to implement MENTUPP									X			X	X	X

The outcome evaluation will examine the effectiveness of the MENTUPP intervention to generate the expected proximate, intermediate, and long-term outcomes. For the economic evaluation, a range of costs will be measured in addition to the proximate, intermediate and long-term outcomes. Participants will be invited to complete the six validated questionnaires and bespoke survey measures at three time intervals: baseline, 6-month follow-up and 9-month follow-up.

### Outcome evaluation

Six validated instruments consisting together of 61 items for the outcome evaluation will be administered to participants:Mental wellbeing and quality of life: The World Health Organisation – Five Wellbeing Index (WHO-5) [67]Depression: Patient Health Questionnaire (PHQ-9) [68]Anxiety: Generalized Anxiety Disorder Scale (GAD-7) [68]Depression Stigma: Depression Stigma Scale (DSS) [69]Burnout: Burnout Assessment Tool (BAT) [70]Presence (level) of psychosocial risk factors, work resources and stressors: 19 items selected from the Copenhagen Psychosocial Questionnaire, Version III (COPSOQ-III) [71]

Two bespoke surveys, a pre- and post-intervention survey, will be used to measure various aspects related to the outcome, process and economic evaluation of the MENTUPP intervention. The pre-intervention survey will be conducted with all participants at baseline and consists of 34 items: sociodemographic and work-related information, experience with mental health difficulties, initial expectations and intentions with regard to MENTUPP, presenteeism and absenteeism, healthcare and mental healthcare use, and proximate and intermediate outcomes of the MENTUPP intervention. The post-intervention survey is conducted with all participants at 6-month and 9-month follow-up and consists of 28 items and overlaps largely with the pre-intervention survey. Data are collected related to the following themes: experience with the MENTUPP Hub, experience with mental health difficulties, presenteeism and absenteeism, healthcare and mental healthcare use, and proximate and intermediate outcomes of the MENTUPP intervention (see Tables 1 and 2 for more information on the measures used).

**Table 2 Tab2:** Overview of evaluation measures and instruments

Type of measure	Measure	Measure description	Time of data collection			Type of evaluation		
			Baseline	6 months	9 months	Outcome	Process	Economic
6 validated scales	WHO-5: wellbeing [63]	The WHO-5 consists of **5 items** measuring mental wellbeing. The questionnaire uses solely positively phrased items (thus no symptom-related language), which participants have to rate on a 6-point Likert scale ranging from 0 to 5	X	X	X	X		X
	PHQ-9: depression [64]	The PHQ-9 consists of **9 items** that measure symptoms of depression over the last two weeks. The items need to be rated on a 4-point Likert scale (i.e. not at all – several days – more than half the days – nearly every day)	X	X	X	X		X
	GAD-7: anxiety [64]	The GAD-7 is a **7-item** scale that measures the presence of anxiety-related problems over the last two weeks. The items need to be rated on a 4-point Likert scale (i.e. not at all – several days – more than half the days – nearly every day). An eighth item assesses the level of difficulty with certain aspects of life due to anxiety-related problems and ranges from 0 (i.e. not difficult at all) to 3 (i.e. extremely difficult)	X	X	X	X		X
	DSS: personal stigma [65]	The personal stigma subscale of The DSS consists of **9 items** and measures respondents’ personal attitudes towards depression. As for the pilot, the items are slightly reformulated and measure attitudes towards depression and anxiety, instead of only attitudes towards depression. This is a common practice and does not affect the validity or reliability of the scale. The items need to be rated on 5-point Likert scale	X	X	X	X		X
	BAT: burnout [66]	The BAT consists of **12 items** and measures 4 dimensions of burnout: exhaustion, mental distance, emotional impairment, cognitive impairment. Contrary to the Maslach Burnout inventory it measures cognitive malfunctioning and produces a single burnout score that is easy to interpret. The items need to be rated on a 5-point Likert scale	X	X	X	X		X
	COPSOQ-III: psychosocial factors in the workplace [67]	Ten psychosocial work environment dimensions^a^ plus three higher-level constructs^b^ measured with a total of **19 items**, are selected to measure the psychosocial environment in MENTUPP. The items are derived from the Copenhagen Psychosocial Questionnaire, version III (COPSOQ-III)	X	X	X	X		X
2 bespoke surveys	Pre-intervention bespoke survey	Two bespoke surveys, a pre- and post-intervention survey, will be used to measure various aspects related to the outcome, process, and economic evaluation of the MENTUPP intervention. The bespoke survey at baseline consists of 34 items	X			X	X	X
	Post-intervention bespoke survey	The bespoke survey completed at 6-month and 9-month follow-up consists of 28 items and overlaps largely with the baseline bespoke survey		X	X	X	X	X
Monitoring instrument	Characteristics of the SME and implementation	A monitoring instrument developed by the MENTUPP consortium will be used to collect information from each SME in close consultation with the main contact person or designated ‘Champion’ to track relevant information about the organisation, the implementation of MENTUPP within the organisation, and cost-related outcomes	X	X	X		X	X
User data	User information on participants’ use of the Hub	Participant User data will be collected within the MENTUPP Hub to provide the frequency (total number) of registration, logins, and visits to pages and intensity (length of time) for the various pages and overall time spent in the Hub		X	X		X	X
Focus group	With ROs	Focus groups will be carried out with the ROs to collect additional information on the implementation process of MENTUPP		X	X		X	

^*^1. Quantitative demands at work (2 items), 2. Work pace (1 item), 3. Influence at work (4 items), 4. Recognition (1 item), 5. Quality of leadership (4 items), 6. Mutual trust between employees (1 items), 7. Trust regarding management (2 items), 8. Justice at work (2 items), 9. Social support from colleagues (1 item), 10. Social support from supervisors (1 item)

^**^Combinations of selected items from the dimensions above will be used to approximate higher-level constructs of work stress (job strain and effort-reward imbalance) [6, 7] and of workplace social capital [72, 73]

### Process evaluation

The process evaluation will be conducted using a combination of the following qualitative and quantitative measures: two bespoke surveys (described above), a monitoring instrument, user data of the MENTUPP Hub users, and a focus group with the local research officers.

A monitoring instrument developed by the MENTUPP consortium will be used to collect information from each of the participating SMEs in close consultation with the main contact person or designated ‘Champion’ to inform the process evaluation. The instrument will track relevant information related to the process evaluation. Information about the organisation at the time of recruitment, including information about mental health-related activities and mental health support for employees in the organisation at the time of recruitment and after implementation of MENTUPP, will be gathered in the monitoring instrument. Furthermore, information on the implementation of MENTUPP in the organisation (events and activities that may impact implementation) and cost-related outcomes at the level of the SME will also be collected.

Pseudonymised log data of the MENTUPP Hub will be extracted at 6-month and 9-month follow-up as part of the process evaluation (feasibility and reach) to provide detail on the intensity and frequency of the use of the MENTUPP Hub online platform.

After the 6-month follow-up, focus groups with local research officers in each country will be conducted to collect more in-depth qualitative information with respect to the implementation process, appropriateness, feasibility, and maintenance of the MENTUPP Hub. During the focus group the following topics will be discussed: experiences regarding the recruitment and participation at the SME and employee level, experience with the implementation process of MENTUPP in the SMEs, country, sector specific characteristics, online format of MENTUPP and barriers and facilitators to implementation.

## Economic evaluation

For the economic evaluation, the six validated scales, the two self-developed surveys, the monitoring instrument and the log data of the MENTUPP Hub users will all be used to conduct a cost-effectiveness and cost-consequence analysis. Costs will be monitored in relation to conducting e-mental health tools and printing of leaflets and posters in all recruited SMEs. Costs in terms of productivity will be monitored via productivity/SME economic and employee turnover, absenteeism and presenteeism in the intervention and control SMEs. Absenteeism will be assessed by both self-report using customised items deduced from the iMTA Productivity Cost Questionnaire [74] and the Client Service Receipt Inventory [75]. The user data from the MENTUPP Hub will also be analysed to establish patterns of using the Hub, total number of visits and total time spent engaging with the content.

## Data management

Qualtrics [76], a General Data Protection Regulation (GDPR) compliant online platform, will be used to collect data from the validated questionnaires and the two self-developed surveys. To allow matching of the data collected of the same subject at multiple timepoints, an anonymous subject-generated identification code (ID-code) will be used [77]. For participants within the control group, the Qualtrics links will be distributed by email from the local research officers. Participants will be asked to answer four neutral questions at the first of the three time points of data collection to generate an anonymous unique ID-code and ensure confidentiality. For participants in the intervention group, the Qualtrics links will be embedded in the registration process for the MENTUPP Hub. When registering for the MENTUPP Hub, participants will be asked to enter a self-chosen 4-digit code and the SME code.

## Data analysis

### Outcome evaluation

The outcomes gathered from the six survey measures will be analysed in linear and logistic mixed effects models. The analyses will incorporate baseline and both follow-up timepoints. Changes to the outcomes will be assessed between the intervention and control groups in these models. Furthermore, descriptive analyses will be conducted on baseline characteristics and both follow-up characteristics to understand the findings from the mixed effects models. Differences between countries will be analysed in accordance with the Aspen/Indigo study [78].

### Process evaluation

Descriptive statistics will be used to analyse numeric data of the process evaluation collected via the monitoring instrument, the bespoke surveys and the user data. Qualitative data coming from the focus groups and the monitoring instrument (open text fields) will be analysed thematically. Data gathered via the focus groups with research officers will be audio recorded, transcribed, translated to English where necessary and analysed via thematic analysis. The process evaluation will be informed by the framework based on the three themes of implementation, mechanisms and context [79].

Adherence data are collected in the intervention group in three ways: via the pre-intervention survey, the post-intervention survey and the log data of the Hub. The pre-intervention survey asks participants to indicate whether they have positive expectations about the intervention at start and are intending to make use of the intervention. In the post-intervention survey, respondents are asked to indicate how much time they spent in the past months on MENTUPP-related activities. Finally, the log data of the Hub allows tracking which respondents registered for the Hub, how many times they visited the Hub, how much time they spent on the Hub and how their Hub visits are spread in time during the implementation period. Exploratory analyses will be conducted on the adherence data and results on the intention of respondents to adhere to the intervention at start, the amount of adherence during the intervention period and subsequent withdrawal from the intervention will be reported in accordance with the 2010 Consolidated Standards of Reporting Trials (CONSORT) statement.

### Economic evaluation

A cost-consequence analysis will be conducted to compare differences in costs and outcomes between the intervention and control groups to be calculated; this allows the costs of delivering and implementing MENTUPP to be compared with the different measures collected in the outcome evaluation. Multiple incremental cost-effectiveness ratios comparing costs with different outcome measures can then be determined.

Three perspectives will be used in the economic evaluation: an employer perspective, a healthcare perspective and a societal perspective. The employer perspective considers the costs of mental health issues that are borne by the employer in terms of productivity loss as indicated from data from the surveys. The costs of implementing the intervention will be calculated from the surveys, the monitoring instrument, and the log data from the MENTUPP Hub users. The healthcare perspective only includes costs that are expended on healthcare services funded by the health system and will be analysed based on usage of data from the surveys. The societal perspective includes all costs borne by the whole of society, including productivity costs or other costs not borne by the health system or the employer. This will include data from the surveys, the log data from the MENTUPP Hub, and the monitoring instrument to consider time investment and routine rather than research-related travel costs associated with implementing MENTUPP.

Data on the resources required to develop and implement MENTUPP are being collected and appropriate unit costs will be attached to time and materials used. Bespoke questionnaires have been designed to collect data from individual participants in the two arms of the trial on health service use at baseline, 6-month and 9-month follow-up periods; this will be compared with outcome data collected for these individuals over the same time periods. Data on changes in workplace productivity, including absenteeism and presenteeism are also being collected. Country-specific unit costs for healthcare service use, as well as country and industry-specific hourly wage rates, will be applied to all service utilisation and productivity impacts. To allow for multi-country comparison, final costs across countries will be converted into purchasing power parity adjusted international dollars for a common price year using the Campbell-Cochrane Economics Methods Groups EPPI-Centre Cost Converter [80].

Differences in mean costs will be compared between the two arms of the trial using bias corrected and accelerated bootstrapping. Incremental cost-effectiveness ratios (ICERs) per change in each of the six main outcomes will be calculated at 6-month and 9-month follow-up points. Statistical uncertainty will be explored through bootstrapping 5000 randomly resampled pairs of costs and each of the six outcomes and cost-effectiveness planes will then be drawn.

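### The stated cost comparison names no baseline term, although the survey-based costs are measured at baseline in both arms; adjusting for them would sharpen the cost differences and ICERs at almost no cost

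*Protocol article*

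**What the plan says.** The Economic evaluation part of the Data analysis section sets out the cost analysis in some detail. The comparison is of means: "Differences in mean costs will be compared between the two arms of the trial using bias corrected and accelerated bootstrapping". On the ratios it says "Incremental cost-effectiveness ratios (ICERs) per change in each of the six main outcomes will be calculated at 6-month and 9-month follow-up points". Uncertainty is explored by "bootstrapping 5000 randomly resampled pairs of costs and each of the six outcomes". None of these sentences mentions a baseline cost.

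The baseline data exist. The same section says that participants in both arms report "health service use at baseline, 6-month and 9-month follow-up periods", and adds: "Data on changes in workplace productivity, including absenteeism and presenteeism are also being collected". Under Outcome evaluation (Data collection), the baseline and follow-up surveys are both said to cover "presenteeism and absenteeism, healthcare and mental healthcare use, and proximate and intermediate outcomes of the MENTUPP intervention". Table 1 marks the survey-based cost items, for example "Absenteeism of employees due to mental health issues", at all three time points. Time on the Hub comes from user data and is marked at 6 and 9 months only.

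For the six survey measures, the Outcome evaluation part of Data analysis states that the mixed models use baseline together with both follow-ups. No matching statement is made for costs.

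**The concern.** What a person cost before the trial usually predicts what that person costs during it. If the baseline value is left out, two things follow. The interval around the cost difference is wider than the collected data require. And whatever difference in baseline cost happens to exist between the arms' responders passes, in proportion to rho, into the cost difference, the ICERs and the cost-effectiveness planes, where it would be read as a cost or saving due to the intervention.

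A baseline difference among responders is plausible here for reasons beyond chance. According to Randomisation of SMEs and Individual recruitment, SMEs are told their allocation before the introductory sessions are scheduled and before individuals consent, and participants are not blinded. The Sample size section then expects 65% attrition. Who joins and who stays could therefore differ by arm.

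**Working it through.** **Inputs from the Sample size section.** 27 SMEs per arm, 23 analysed participants per SME, 621 per arm, ICC 0.05, difference 0.25 SD, two-sided 0.05, stated power 85%.

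**The plan's own figure.** Design effect = 1 + (23 − 1) × 0.05 = 2.10. Effective n per arm = 621 / 2.10 = 295.7. Power is 86.0% by the normal approximation and 84.7% by a noncentral t with 52 df, so the stated 85% reproduces. That figure concerns the difference in mean change. The plan sets no power for costs, so none is calculated for them here.

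**Inputs assumed.** Rho is not given; the range 0.2 to 0.7 is used. The ICC of costs is taken as 0.05, rho as equal between and within SMEs, and the cost SD as equal at baseline and follow-up.

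**Formulas, in SD units of cost.**
- Unadjusted SE of the arm difference = √(2 × 2.10 / 621) = 0.082.
- Adjusted SE = 0.082 × √(1 − rho²).
- Shift in the unadjusted difference = rho × realised baseline difference. It is shown for a baseline difference of one SE (0.082) and of 1.96 SE (0.161).
- Variance relative to the unadjusted comparison: 1 − rho² for regression on baseline, 2(1 − rho) for a change score.

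| rho | Adjusted SE | SE reduction | Shift, 1 SE | Shift, 1.96 SE | Variance ratio, regression | Variance ratio, change score |
|---|---|---|---|---|---|---|
| 0.2 | 0.081 | 2% | 0.016 | 0.032 | 0.96 | 1.60 |
| 0.3 | 0.078 | 5% | 0.025 | 0.048 | 0.91 | 1.40 |
| 0.5 | 0.071 | 13% | 0.041 | 0.081 | 0.75 | 1.00 |
| 0.7 | 0.059 | 29% | 0.058 | 0.113 | 0.51 | 0.60 |

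**Skewed costs.** A simulation of clustered lognormal costs (2,000 runs per setting, no true difference) gave adjusted-to-unadjusted SE ratios of 0.97, 0.92 and 0.77 at log-scale correlations of 0.3, 0.5 and 0.7, that is, reductions of about 3%, 8% and 23%. Both estimators were centred on zero. The gain is smaller because a given log-scale correlation is weaker on the cost scale: with unit log variance, 0.5 becomes (e^0.5 − 1)/(e − 1) = 0.38, and √(1 − 0.38²) = 0.92.

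**The case against.** The strongest objection is that silence is not a decision. A reader might infer that the plan has chosen a raw comparison and ruled adjustment out. The text says neither. Bias-corrected and accelerated bootstrapping can be applied to an adjusted difference, a condensed article often leaves covariates to a fuller plan, and the reference to changes in workplace productivity may hint that baseline is used. This stands as a limit on the claim. It does not remove the point: the article fixes the estimate, the interval method, the number of resamples and what is resampled, and a baseline term is absent from all of them. If change scores are meant, they do worse than the unadjusted comparison when rho is below 0.5.

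Other stronger readings also fail:

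- **Bias.** A reader might infer that the cost difference is biased. Chance imbalance under randomisation is not bias in expectation, and a properly formed unadjusted interval already reflects it.
- **Mismatch within the ICER.** A reader might infer that the denominator is baseline-corrected and the numerator is not. An ICER per change in outcome can simply mean cost per unit of incremental effect.
- **High rho from country prices.** Country-specific unit costs and wage rates enter both baseline and follow-up costs. But SMEs are allocated in pairs within sector and country, so much of that component is balanced between arms, apart from unequal responder numbers and unpaired SMEs. The chance SE of 0.082 ignores this pairing and may be too large for that part of the cost.
- **All costs.** Hub time has no baseline collection, and delivery costs have no true pre-intervention counterpart. The point covers survey-based costs only.

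**Conclusion.** The point holds as a worthwhile improvement to a stated method; it does not show that the planned analysis is invalid. As written, the cost comparison names no baseline term for costs measured at baseline in both arms.

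The precision gain depends on a correlation that the document does not give. It is small at rho 0.2 to 0.3 (SE lower by 2% to 5%), moderate at 0.5 (13%) and large at 0.7 (29%), with smaller gains under skew if those values describe log costs. A one-SE baseline difference shifts the unadjusted cost difference by 0.016 to 0.058 SD over the same range.

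The second benefit is protection against a realised difference among responders, which could be systematic given recruitment after allocation is known and the expected attrition. Adjustment removes only the part of such a difference that baseline cost predicts.

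**What to change.** In the Economic evaluation part of Data analysis, state the following:

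- In each bootstrap replicate, incremental survey-based cost is the arm coefficient from a regression of follow-up cost on arm and the participant's own baseline cost, for the same cost category and perspective.
- In the same replicate, incremental effect is estimated with adjustment for the baseline value of the outcome.
- These adjusted pairs supply the intervals, the ICERs and the cost-effectiveness planes.
- Delivery and Hub-time costs, which have no pre-intervention value, are added to the follow-up side without adjustment.
- The unadjusted difference in mean costs is reported as a sensitivity analysis.

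If a fuller plan already does this, a sentence in the article saying so is enough.

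The change needs a short addition to the text and regressions inside the planned bootstrap loop, with no new data or participants. There are two small drawbacks: a missing baseline cost needs a simple imputation, and the headline incremental cost will no longer equal the difference between two tabulated means.
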